**Figure 1 F1:**
[figure not shown]
Trial design, procedures, stages and data collection.

### Randomization and allocation procedures

Subjects will be allocated through central, computerized randomization utilizing a stratified permuted-block randomization employing random block sizes. After confirming eligibility and completion of baseline data collection, the Study Coordinator will contact the designated investigator ([name]) for allocation. He will consult the prepared block randomized list and the next allocation contained in sealed opaque envelope will be given to the treatment provider, while also recording the subject ID number to allow for ascertainment of compliance with treatment allocation. The three treatment arms are labeled using letters “L”, “W” and “E” and correspond to a labeled device. The names of particular devices will not be used. The treatment provider will open the envelope and provide the assigned treatment device to the participant. Block stratification will be performed for opioid use (current vs. past/never) and workers’ compensation claim (yes vs. no).

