### Statistical approach

#### Statistical power/Sample size

Sample size determination is based on the comparisons of the study arms for the primary outcome variable, ODI. In previous studies of low back pain patients , the baseline ODI values for one study group were mean (SD) of 60.2 (15.0) and for a second study group were 59.9 (14.4) [39,40]. The total score for the ODI is a percentage, ranging from 0 to 100. It is suggested that the reliability of the ODI requires a minimum detectable change of at least 10 points, as any smaller difference may be attributable to error in the measurement [25]. Assuming equality of the study arms at baseline, which can be assured by adjusting for baseline ODI in the regression model, and a minimal detectable effect size of a 10 point difference on the post-treatment value, sample size is based on a comparison of mean (SD) of 60 (15) vs. 50 (15), a 17% relative difference post treatment, using a two-sided comparison with alpha of 0.025 to allow for multiplicity adjustment. Under these assumptions, a sample size of n = 43 subjects per study arm is required to achieve 80% power. However, it is expected that the stimulation arms will produce at least a 25% relative improvement over the control arm. Assuming 60 (15) vs. 45 (15), a 25% relative difference, using a two-sided alpha 0.025 comparison, a sample size of n = 20 subjects per study arm is required for 80% power, or n = 25 subjects for 90% power. Allowing for a 20% dropout rate, a sample size of n = 38 subjects will be enrolled in each study arm to provide n = 25 evaluable subjects for data analysis.

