### Statistical analysis

#### Primary analysis

The primary analysis is the comparison of the three study arms on the primary outcome, Oswestry Disability Index (ODI). Given that repeated measurements are collected, a mixed effects linear regression model will be fitted with an unstructured covariance matrix to account for lack of independence introduced by the repeated measurements. In this model, the repeated measurements are nested within study subject (weeks 0, or baseline, and weeks 1, 4, 8, and 12). The primary predictor is study group. A time variable will be included as a covariate, since visits will not always be at the planned intervals. Other covariates will be assessed for possible confounding in the relationship between treatment arm and outcome. It is likely that the pattern of dropouts will vary between the study groups, where the study interventions that are most effective having the dropouts later on in the follow-up, while the intervention least effective to have dropouts early on. The analysis will emphasize the 4-week time point as the primary end point, which ends the intensive intervention period. At 4 weeks compliance to the protocol and complete follow-up should be at a maximum. The remaining time to 12 weeks will measure long term effectiveness and acceptance of the study interventions.

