#### Co-variates

Age, gender, tobacco, undiagnosed anxiety, undiagnosed depression, past back pain history, prior and current NSAID use, rescue acetaminophen use.

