#### Post-hoc analyses

Post-hoc analyses will be conducted to attempt to ascertain what factors predicted better responders among the two treatment arms. Potential prognostic factors include gender, tobacco, anxiety, depression, (age and past back pain history will be assessed for residual confounding, but controlled in study design), belief in effectiveness of the treatments, NSAID use, rescue acetaminophen use.

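### Randomisation is stratified by opioid use and workers' compensation, but neither factor is in the stated covariates; if they predict ODI, the analysis will be mildly conservative

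*Protocol article*

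**What the plan says.** Under Randomization and allocation procedures: "Block stratification will be performed for opioid use (current vs. past/never"; the same sentence adds workers' compensation claim (yes or no) as the second factor. With two levels each, this makes four strata. The abstract names the same two factors.

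Under Primary analysis, "a mixed effects linear regression model will be fitted with an unstructured covariance matrix"; study group is the main predictor and time is a covariate. The rule for anything further is: "Other covariates will be assessed for possible confounding in the relationship between treatment arm and outcome". The sample-size section presents equality of the arms at baseline as something "which can be assured by adjusting for baseline ODI in the regression model".

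The section headed Co-variates reads in full: "Age, gender, tobacco, undiagnosed anxiety, undiagnosed depression, past back pain history, prior and current NSAID use, rescue acetaminophen use".

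Neither stratification factor is named in any of these analysis sections or among the prognostic factors under Post-hoc analyses. No statement says that the analysis will account for the strata. The main secondary endpoint, pain VAS, is to be analysed with the same longitudinal model as ODI.

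**The concern.** Stratified permuted blocks make the arms alike on the two factors. If those factors predict the outcome, the treatment difference varies less from one randomisation to the next than it would under unstratified allocation. A model that omits the factors cannot see this: it leaves their contribution in the residual variance and reports the larger, unstratified standard error. Confidence intervals are then wider than they need to be, the test runs below its nominal level, and power is lower than the same data could give.

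The article's entry rule is unlikely to repair this. A screen for confounding looks for covariates related to both arm and outcome. Stratification weakens the link with arm, so the screen would tend to pass over the two variables the design singled out. The list names two other analgesic variables (NSAID and rescue acetaminophen use) but not opioid use, the one used to stratify.

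**Working it through.** **Inputs from the protocol article.** SD 15. Differences of 10 points (minimal detectable) and 15 points (expected). Planning level: "using a two-sided comparison with alpha of 0.025 to allow for multiplicity adjustment". 25 evaluable per arm is the planned number. 38 enrolled per arm with the stated 20% dropout gives 38 × 0.8 = 30.4, so 30 per arm is also shown.

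**Assumed input.** R², the share of residual ODI variance (after baseline ODI) explained by the two factors. The article gives no figure. The range 0 to 15% is used; with baseline ODI in the model, 0 to 10% is the more plausible part.

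**Step 1: reproduce the plan's figures.** n per arm = 2(z₀.₉₈₇₅ + z_power)² (SD/δ)², with z₀.₉₈₇₅ = 2.2414.
- 10 points, 80% power: 2(2.2414 + 0.8416)² × 2.25 = 42.8, so 43.
- 15 points, 80% power: 2(2.2414 + 0.8416)² × 1 = 19.01, so 20.
- 15 points, 90% power: 2(2.2414 + 1.2816)² × 1 = 24.8, so 25.

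All three match the article.

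**Step 2: effect of leaving the strata out.** Let SE₀ = 15√(2/n) be the standard error reported without the strata. With the strata balanced by design, the true standard error is SE₀√(1−R²). Then:
- reported/true SE = 1/√(1−R²)
- actual level = 2[1 − Φ(2.2414/√(1−R²))]
- power without strata = Φ((δ − 2.2414·SE₀)/(SE₀√(1−R²)))
- power with strata = Φ(δ/(SE₀√(1−R²)) − 2.2414)

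Example: n = 30, δ = 10, R² = 0.15. SE₀ = 3.873 and the true SE is 3.873 × 0.922 = 3.571. Without: (10 − 8.681)/3.571 = 0.369, so 64.4%. With: 10/3.571 − 2.241 = 0.559, so 71.2%.

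| R² | Reported/true SE | Actual level of 2.5% test | Power, 15 points, 25 per arm: without / with | Power, 10 points, 30 per arm: without / with |
|---|---|---|---|---|
| 0 | 1.000 | 2.50% | 90.2 / 90.2% | 63.3 / 63.3% |
| 5% | 1.026 | 2.15% | 90.8 / 91.7% | 63.7 / 65.8% |
| 10% | 1.054 | 1.81% | 91.4 / 93.1% | 64.0 / 68.4% |
| 15% | 1.085 | 1.51% | 92.0 / 94.4% | 64.4 / 71.2% |

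**Step 3: check by simulation.** Step 2 assumes exact balance, which incomplete blocks in four strata do not give. A simulation used three arms, blocks of 3 or 6, one time point, 6,000 runs per setting, and assumed prevalences of 30% opioid use and 20% workers' compensation. Results for 75 patients (25 per arm):
- R² = 0: leaving the factors out made no difference.
- R² = 0.10, factors omitted: empirical SE 4.01 against 4.24 reported; type I error 0.038 at nominal 0.05.
- R² = 0.10, factors included: empirical SE 3.99 against 4.02 reported; type I error 0.049.

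At R² = 0.05 the effect is too small to show cleanly. The simulation error of a 2.5% rate is √(0.025 × 0.975/6000) = 0.002, and the omitted-factor rates were 0.021 with 75 patients and 0.025 with 114.

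**The case against.** The strongest reply is that the full list of model terms commonly belongs in an SAP, and this is a condensed article. The Co-variates section is a bare list that does not claim to be closed. It also omits baseline ODI, which the sample-size section treats as a model term. The abstract allows adjustment as needed, and nothing says the strata will be excluded. That much stands: the article does not rule the strata out. But it is not silent either. It commits to a list and an entry rule, and both point away from the stratification factors.

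Several stronger readings are tempting and are not supported:
- **That the standard errors are too large as a matter of fact.** This holds only if the factors predict ODI beyond baseline ODI and the listed covariates. At R² = 0 nothing changes.
- **That the precision gained by stratifying is lost.** The balance and the smaller true variance of the estimate remain. What is forgone is the narrower interval and higher power an adjusted model would report. Power without the strata does not fall as R² rises; it only fails to rise as far.
- **That the screen is bound to exclude them.** The article gives no criterion. Incomplete blocks and the dropout differences between arms that it expects could leave some imbalance in the analysed set.
- **That the remark under Post-hoc analyses is part of the problem**, where "age and past back pain history will be assessed for residual confounding, but controlled in study design". Neither variable is a stratification factor, but the eligibility limits on age and pain duration are a weak form of design control, and that section does not govern the primary model.

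**Conclusion.** The mismatch between the randomisation and the stated covariates is real; its consequence is conditional and modest. For R² between 0 and 15%, reported standard errors are 0 to about 8% too large and the nominal 2.5% test runs at 2.5% down to about 1.5%. An adjusted model would have up to 71.2 − 64.4 = 6.8 points more power for a 10-point difference at 30 per arm. For the effect the trial is sized on (15 points, 25 per arm), the gain is 0.9 points at R² = 5% and 1.7 points at 10%.

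A reader might infer a threat to the trial's validity or to its planned power. The figures show neither: the omission does not bias the comparison, the error is conservative, and power at 15 points stays at or above 90% throughout the range. The size rests on the assumed R², the planning SD of 15, near-complete balance within strata, and a single-time-point approximation to the mixed model.

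**What to change.** State under Primary analysis and Co-variates that opioid use (current against past or never) and workers' compensation claim (yes/no) enter the primary ODI model as fixed effects, whatever any assessment of confounding shows. Say the same for the main secondary model for pain VAS.

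Both factors have to be known before a patient can be allocated, so no new data are needed. The cost is one sentence in the plan and two degrees of freedom in each model.

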### Blinding

We will attempt to blind patients and assessors to achieve double blinding. Patients will not be told what electrotherapy techniques are being utilized in this study, only that there are two active electrotherapies out of the spectrum of electrotherapy devices and a sham group. All study materials will be void of the words H-Wave® or TENS. Patient blinding will be accomplished by providing all patients either a H-Wave® device, a fully operation TENS Unit modified to function within a H-Wave® device housing, or a sham electrotherapy device with minimally perceptible electrical current output modified to function within a H-Wave® device housing. Researchers providing the treatment are not blinded. Assessors are blinded and will not be present for the intervention. Participants will be instructed not to reveal or discuss the type of treatment characteristics they are experiencing.

Sham devices will appear to operate in the same exact way as a fully functional electrotherapy device, including battery drain and usage log. At maximal settings, weak electrical current will be flowing to the pads so that the patients may perceive the device as active treatment.

Additional blinding of subjects or treatment within this trial is not possible. The research team will be required to wear color-coded nametags indicating whether or not the researcher is blinded or non-blinded to avoid any confusion at the time of assessments. Efficacy of assessor blinding will be conducted at all onsite assessments by recording assessor’s opinion of treatment arm for each subject.

### Outcome measures

Outcome measures will be assessed at baseline, 1 week, 4 weeks, 8 weeks, and 12 weeks, with the primary outcome being at 4 weeks. Assessment will occur in the same manner and at the same time intervals for all treatment arms utilizing standardized methods. Treatment failure will be defined as if patient terminates assigned treatment arm for non-efficacy or election to pursue surgical or invasive procedure or other excluded cointerventions.

The primary outcome measure will be the Oswestry Disability Index (ODI). The ODI is widely used in low back pain intervention trials, and provides a measure of functional improvement The ODI was selected compared to a subjective pain rating [25-29]. Secondary outcome measures include Rowland Morris Instrument (0–24 scale of disability); VAS Pain score (0–100); physical activity levels objectively measured using accelerometers worn by participants during waking hours over during the entire 12 week study period; functional capacity evaluation including strength when pushing and pulling (3 repetitions lasting 5 seconds each of both pushing and pulling measuring both peak and average kg of force according to standard EvalTech Functional Systems protocol which utilizes a load cell to measure forces exerted); range of lumbar spine motion (up to participants maximum range of specific movement) in flexion, extension, lateral rotation; duration of time (minutes) sitting comfortably (subjective estimate made by participant during questionnaire); duration of time (minutes) standing comfortably (subjective estimate made by participant during questionnaire); duration (minutes) and distance (meters) walking comfortably (subjective estimate made by participant during questionnaire); summed VAS pain × days rating; days of impairment (days); lost workdays (days); time to exacerbation (days until increase 3/10 pain); rescue acetaminophen tablets consumed (% and number); NSAID discontinuation (%); opioid discontinuation (%). The pain VAS score is assessed immediately before and after treatment at weeks 0, 1, and daily scores pre and post home-treatment in a diary that the participant keeps (Table 1).

**Table 1 T1:** Outcome measures

	

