**Secondary measures:**	
a.	Rowland Morris Instrument (0–24 scale of disability)
b.	VAS Pain score (0–10)
c.	Physical activity levels (objectively measured using accelerometers)
d.	Functional evaluation including strength when pushing (peak and average kg of force)
e.	Functional evaluation including strength when pulling (peak and average kg of force)
f.	Comfortable (up to maximum baseline pain level) range of motion in flexion (degrees from neutral)
g.	Comfortable (up to maximum baseline pain level) range of motion in extension (degrees from neutral)
h.	Duration of time sitting comfortably (up to maximum baseline pain level) (minutes)
i.	Duration of time standing comfortably (up to maximum baseline pain level) (minutes)
j.	Duration and distance walking comfortably (up to maximum baseline pain level) (minutes and meters)
k.	Summed VAS pain × days rating
l.	Days of impairment (days)
m.	Lost workdays (days)
n.	Time to exacerbation (days until increase 3/10 pain)
o.	Rescue acetaminophen tablets consumed (% and number)
p.	NSAID discontinuation (%)
q.	Opioid discontinuation (%)

Functional assessments will be completed using a standardized protocol on a BTE EvalTech system. Standard protocols for Lumbar Flexion/Extension, Lumbar Lateral Flexion, Shoulder Height Push and Pull, Cart Height Push and Pull are used. Researchers performing assessments are trained to perform all assessments exactly the same following the BTE EvalTtech protocol (Figure 2).

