### Assessments

Timing of assessments is identical in each arm. Assessments will be conducted by blinded assessors. Enrollment, randomization and initial treatment will occur at the time of enrollment. All participants will return 1 week after initial treatment for assessment of subject ability to correctly use their assigned device; have questions answered about the protocol, and to complete week 1 assessment. Subjective assessments will be measured at baseline, 1 week, 4 weeks, 8 weeks, and 12 weeks. Objective assessments will be measured pre and post-treatment at baseline and post-treatment at week 1, week 4, and week 12. No treatments are provided by the researchers after week 1, although patients will be performing home treatments per protocol for the entire 12 week period. Compliance will be assessed using digital time data logs recorded automatically by each device and diaries kept by participants. Participants in each arm will have identical and comparable contact time with providers and assessors to minimize treatment bias. All participants will be contacted weekly by a blinded assessor via telephone to encourage compliance and use of daily treatment diaries.

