### Treatment protocols

Subjects will be allocated to one of the three arms. Each treatment arm will have identical numbers of visits and contact time. Each arm will receive the uniform instructions for using of their assigned electrotherapy device. Patients will be instructed to use their assigned device daily upon waking and before bedtime, and up to two additional treatments during the day as needed (e.g., 4 1-hour treatment sessions). Providers will place electrodes and activate the device as per the protocol for each arm. Patients will be told that it is possible to not immediately feel effects of electrical treatment due to current levels that do not meet sensory thresholds. Patients will return after 1 week for reevaluation on electrode placement and ability to achieve the required self-administered stimulation levels. Providers are trained in standardized fashion to educate each participant on their assigned therapy.

The H-Wave® device delivers electrical stimulation through the placement of 4 electrode pads in a rectangular geometric pattern at the circumference of the low back pain nidus. Patients will be instructed on optimal electrode placement for home use. The H-Wave® Device is controlled by the patient after instruction from a therapist or practitioner. The stimulation parameters in terms of pulse duration and frequency are proprietary for the manufacturer and thus are not included in this protocol. However, the maximal intensity offered by the device is the goal of the treatment intensity. Patients are instructed to achieve the highest intensity possible in graduated fashion. Lower intensities are accepted if the patient cannot comfortably reach the maximal device intensity and will be noted on diary logs. There are controls for intensity and frequency, which the patient manipulates according to specific instructions and tolerances. Patients in this arm will be required to reach near maximal intensity on low frequency. The maximal intensity may, in rare cases, induce transient muscular contractions. Patients are instructed not to increase the intensity to a painful level. The treatment is then self-administered for the duration of the study.

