### Compliance

Compliance will be assessed by device logs and diaries. Each device will be capable of recording treatment applications and duration, and will be downloaded electronically at each in-person assessment. Total treatment time of 3.5 hours per week will be set as the threshold for compliance. If VAS Pain drops to a daily average of less than or equal to 2 out of 10, patients will be considered in compliance regardless of the number of treatments completed on that day. Patients will be called once per week to promote compliance and answer any questions.

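### Diary pain scores are timed around device sessions, so two day-level secondary outcomes and the daily-average compliance rule may have no score on days without a session

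*Protocol article*

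**What the plan says.** Under Outcome measures, the pain VAS has two stated timings. In the clinic: "The pain VAS score is assessed immediately before and after treatment at weeks 0, 1". At home: "daily scores pre and post home-treatment in a diary that the participant keeps". The Assessments section refers to the diaries as treatment diaries and has participants reminded of them by weekly telephone calls.

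Table 1 lists two secondary outcomes that need pain by day: summed VAS pain × days, and "Time to exacerbation (days until increase 3/10 pain"). The article does not name their data source.

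Under Treatment protocols, patients use the device on waking and before bed, with "up to two additional treatments during the day as needed". Under Compliance, the threshold is 3.5 hours per week. If the daily average VAS is 2 or less, "patients will be considered in compliance regardless of the number of treatments completed on that day".

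Separately, the general schedule reads "Outcome measures will be assessed at baseline, 1 week, 4 weeks, 8 weeks, and 12 weeks, with the primary outcome being at 4 weeks". Assessments adds: "Subjective assessments will be measured at baseline, 1 week, 4 weeks, 8 weeks, and 12 weeks". Neither statement depends on device use. Secondary analyses names VAS change to each follow-up visit as the main secondary endpoint.

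**The concern.** The stated trigger for a diary score is a home session. A patient who skips the device for a day, or stops it but stays in follow-up, has no scheduled diary score from then on. Whether a patient uses the device plausibly depends on pain, in both directions: some stop because it does not help, and others skip because they feel well. Gaps in the diary would then carry information about the very quantity it measures.

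The plan wants such patients followed. Discontinuation encourages continued follow-up, and Other considerations analyses patients by assignment irrespective of compliance. Stopping for non-efficacy is anticipated, since Outcome measures counts it as treatment failure. At stake are the two day-level outcomes and the low-pain exemption in the compliance rule. A score the diary never asked for cannot be recovered by a later analysis plan.

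**Working it through.** No figure in the article has to be reproduced for this point. The check sets the sections side by side and then illustrates the size with assumed values.

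**1. Which quantities depend on the diary?**
- ODI at weeks 1, 4, 8 and 12: scheduled visits or, at week 8, a call. Independent of device use.
- VAS change to each follow-up visit: covered by the same general schedule. Independent of device use.
- Summed VAS × days and time to exacerbation in days: both need day-level pain. The diary is the only day-level pain source described. After week 1 the visits are three or four weeks apart and cannot date a flare to the day.
- Daily-average VAS for compliance: needs a score on the day in question, whatever the number of sessions.

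**2. Can session-free days occur in compliant patients?** Yes. Treatment protocols gives one-hour sessions as its example, and the threshold is 3.5 hours per week, so four sessions suffice (4 × 1 = 4 hours). One per day leaves 7 − 4 = 3 days of the week without a session; two per day leaves 7 − 2 = 5. The low-pain exemption places no lower limit on the sessions completed that day.

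**3. Do Outcome measures and Compliance fit together?** Not as written. The first ties the score to a session. The second uses a daily average whatever the session count, including zero.

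**4. Illustration for summed VAS × days** (assumed: 84 days, constant VAS, one value per day, unrecorded days add nothing).
- VAS 6, all days recorded: 6 × 84 = 504.
- VAS 6, diary ends at day 28: 6 × 28 = 168.
- Improved to VAS 3, all days recorded: 3 × 84 = 252. The non-improver who stopped would look better than this patient.
- Two arms, both truly at VAS 6. With 10% stopping at day 28: 0.9 × 504 + 0.1 × 168 = 470.4. With 30%: 0.7 × 504 + 0.3 × 168 = 403.2. Spurious gap: 67.2, or 67.2/504 = 13%, in favour of the arm with more stopping.
- With 20% stopping in both arms: 436.8 in each, gap 0.

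**5. Illustration for the mean of recorded scores** (assumed values).
- Continuers at VAS 4, stoppers at VAS 6. The late diary mean reads 4.0. The true mean is 0.9 × 4 + 0.1 × 6 = 4.2 with 10% stopped, 4.4 with 20% and 4.6 with 30%. The diary understates pain.
- One patient with half of days at VAS 2 and half at VAS 5: true mean 3.5. If half of the low-pain days are skipped, the diary mean is (0.25 × 2 + 0.5 × 5)/0.75 = 4.0. The diary overstates pain.

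The direction therefore depends on who skips and on how unrecorded days are scored.

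**The case against.** The strongest reply is that the article never says scores are recorded only around sessions. The compliance rule, with its daily average at any session count, may show that a score was intended every day, and a condensed article can leave diary layout to the full protocol. This has force: the restriction is inferred from the one stated timing. But that timing is a statement rather than a silence, and it does not fit the compliance rule. One of the two sections needs amending on either reading.

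A reader might go further and infer that a patient who stops the device yields no more pain data, so that the trial's pain comparison is biased. The article does not support that. The VAS sentence names only weeks 0 and 1 for clinic scores around treatment, but VAS is a listed outcome and the general schedule covers weeks 4, 8 and 12 regardless of device use.

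A reader might also infer that the plan predicts more device stopping in the weaker arm. Primary analysis says "It is likely that the pattern of dropouts will vary between the study groups", but this concerns dropouts, not patients who stop the device and stay in follow-up. How common the latter are, and whether they differ by arm, is not stated. A fixed-time diary would not recover data from true dropouts.

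Two further limits stand. The two outcomes are among 17 lettered items in Table 1 and are not among the key comparisons in Secondary analyses. And since pre- and post-session scores are distinguishable, an analysis could use pre-session values alone. That would deal with the transient effect of stimulation, but not with days that have no score.

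**Conclusion.** The point holds in a limited form. As written, the diary schedule leaves session-free days and the period after stopping without a scheduled pain score. This puts summed VAS × days and time to exacerbation at risk of missing data related to pain and to treatment stopping, and it leaves the daily-average compliance rule without an input on such days.

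The conclusion assumes that the diary is the source for the two outcomes, which is reasonable because no other day-level source is described, and that it is completed as stated. Bias between arms is a risk, not an established fact. It requires skipping or stopping that differs by arm, and it can go either way. The gap of 67 points (13%) and the shifts in the diary mean are illustrations with assumed values, not estimates for this trial. The primary ODI analysis and the main secondary VAS analysis are unaffected. This is a worthwhile, inexpensive improvement and not a threat to the main conclusions.

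**What to change.** In Outcome measures, state that the diary VAS is recorded at fixed times every day, for example on waking and at bedtime and before any session at that time, to the end of week 12, whether or not the device is used and also after it has been stopped. Derive summed VAS × days, time to exacerbation and the daily average in the Compliance section from these fixed-time scores only. Keep post-session scores as a separate measure of acute response. This reconciles the two sections. The existing weekly call can prompt patients who have stopped the device to keep up the diary.

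The cost is a changed diary template and a few extra entries on days without a session. The suggested times match the two instructed daily sessions, so the burden on regular users hardly changes. No visit is added and no treatment rule is altered.
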